#### Safety and tolerability

At T0 and T1, participants complete a baseline and follow-up tDCS tolerability questionnaire, which assesses their experience with the stimulation and their assumption of group membership. At each tDCS session, a full body 16-item systems questionnaire and the NIBS tolerability questionnaire will be completed by the participant and parent to assess the participant’s tolerability of tDCS and to monitor any side effects or adverse events [58–60]. Adverse event (AE) monitoring will begin at the baseline assessment and continue through the study timeline. All AEs will be evaluated by the study physician for seriousness, severity, expectedness, and relatedness to the intervention, using a validated AE worksheet (see Appendix).

#### Acceptability and device usability

To evaluate acceptability, a treatment satisfaction scale will be administered at T1. This survey asks participants to rate how helpful they found the tDCS to be, and if they would recommend it to others, as well as open-ended questions about how the tDCS experience can be improved [61]. The standard device training will be video-recorded at T0 for usability analysis. A pre-treatment (T0) and post-treatment (T1) usability survey will also be administered to understand any barriers to using the take-home tDCS device (developed based on the system usability scale [62, 63]). The pre-treatment survey will be used to understand the caregiver’s familiarity with technology in a general sense [64]. At T2, a semi-structured interview will be administered to gain a deeper understanding of participants’ experiences with the tDCS device.

### Secondary outcome measures

Secondary objectives include (i) estimating the probable effect of tDCS on clinical, cognitive (Go/NoGo), and neural (fMRI, DTI) self-regulation outcomes; (ii) exploring the factors influencing outcomes; (iii) exploring the factors influencing participation/refusal. Outcomes will be measured at baseline (T0), week 6 (T1), and week 18 (T2) by blind assessors and data analysts. tDCS sessions occur during weeks 1–3.

#### Clinical

The CGI severity [65] and improvement assessments include an interview by the physician with the participant and caregiver. Parent-reported measures include the Aberrant Behaviour Checklist (ABC) [66, 67], Emotional Dysregulation Inventory (EDI) [68, 69], Autism Impact Measure (AIM) [70], and Emotional Regulation Checklist (ERC) [71]. These measures have been validated in youth with ASD and will indicate clinical treatment-related improvement. The ABC has excellent reliability and was specifically designed to measure treatment effects on aberrant behaviors, with extensive application in previous ASD trials [72]. The EDI-reactivity scale measures poorly regulated negative emotions, and the EDI-dysphoria scale measures minimal positive affect and motivation. The AIM measures treatment-related improvements in children with ASD across several ASD symptom domains [70]. The ERC measures emotional regulation and is sensitive to a broad range of regulatory processes [73].

#### Cognitive

The PsyToolkit Go/No Go task will be used to measure response inhibition. Performance on the Go/No Go task is measured by response time and accuracy [74]. This specific Go/No Go task was chosen due to its simplicity and ability to be understood by individuals with a wide range of IQs and autism severity.

#### Neural

At the baseline assessment (T0), participants will undergo optional high-resolution MRI on a Siemens 3 T Prisma MRI. Structural T1-MPRAGE, DTI, and resting-state functional MRI data will be collected at all time points (T0–T2). Acquisition of neuroimaging data will allow for the investigation of changes at immediate post-treatment (T1) and maintenance at long-term follow-up (T2).

At the baseline assessment, participants will undergo an optional high-resolution MRI on a Siemens 3 T Prisma MRI. Structural (T1 and diffusion tensor imaging) and resting-state functional MRI data will be collected at all timepoints. Acquisition of neuroimaging data will allow for the investigation of changes at immediate post-treatment and maintenance at long-term follow-up.

### Data safety and sharing

#### Data management

All research data will be de-identified. All participants will be given a unique code that will be linked to their personal information accessible only by the research team. All identifiable information will be kept confidential and stored and locked in a secure place that only the study staff will be able to access. Electronic files will be stored securely on hospital or institutionally approved networks or securely on any hospital or institutionally approved portable electronic devices. Research results will be shared through journal publications, academic conferences, and knowledge translation activities at Holland Bloorview. Research assistants and the principal study investigator will have access to the final participant dataset. Protocol amendments will be submitted directly to the REB for review. Once accepted, changes will be communicated to participants directly by the study members.

#### Data safety monitoring

A data safety monitoring committee will meet regularly to review all adverse event reports and study progress every 6 months. The committee will be chaired by a physician and membership will include a scientist, nurse, and lay person/family leader. All adverse events (AE) will be monitored by a safety monitoring committee (SMC) acting independently of the investigators. This SMC will consist of a pediatrician, a methodologist/researcher, and a nurse. This committee will examine all AE reports to ensure that harm is not occurring. The SMC will decide whether the trial needs to be stopped based on rules that they will set at their first meeting in accordance with the documented risks of tDCS. Participant symptoms and safety will be tracked during and after each tDCS session, and all adverse events reported via an REB-approved standard process to an independent in-house safety monitoring committee. Stopping rules for the study based on adverse events will be in place as determined by the SMC. Participants will also be given an emergency number that is monitored by a physician on the study team.

#### Stopping guidelines

At each tDCS session, the study personnel will monitor the participant’s symptoms by completing the systems questionnaire and the NIBS safety and tolerability form. The study personnel will monitor any symptoms (e.g., headache) after the tDCS by having them rate any symptoms on a scale of 1–5. If any symptoms last longer than 15 min graded at 4 or greater, even upon discontinuing tDCS, stopping protocols will be initiated. In the event of a new onset of neurological symptoms, such as severe headache or nausea, the session will be stopped immediately, and the family will be advised to seek immediate medical attention.

If the study personnel, study investigator, or child/parent has any concerns about starting or continuing with a treatment session, the session will be put on hold. Study personnel made aware of any concerns will report them to the study investigator and study physician. The study physician will determine whether the complaint warrants medical attention or adjustment of the treatment. If the severity does not warrant medical treatment, several monitoring and prophylactic measures will be taken. They will be informed that they will be called by our study personnel the next day to get a progress update. Parent concerns at that point will be directed to their family physician to be checked.

### Data analysis

#### Primary measures analysis

##### Feasibility

Feasibility measures will be analyzed as per the progression criteria outlined in Table 1. These criteria were determined based on recommendations by Avery et al. to assess whether to proceed with a full-scale RCT [75]. Associations between participant characteristics (e.g., age, IQ, travel distance) and ability to complete all trial tasks will be examined to inform the planning of a large-scale RCT. *T*-tests will be conducted for associations with continuous variables (e.g., IQ, age, travel distance). Chi-squared tests will be conducted for associations with categorical variables (e.g., gender).

**Table 1 Tab1:** Progression criteria for feasibility metrics

	**GO–proceed with RCT**	**AMEND–proceed with changes**	**STOP–do not proceed unless changes are possible**
Recruitment target	*n* = 46	*n* = 36–45	*n* < 36
Adherence	≥ 90% of tDCS sessions are completed by participants who complete all assessments	70–89% of tDCS sessions are completed by participants who complete all assessments	< 70% of tDCS sessions are completed by participants who complete all assessments
Participant retention	≥ 90% retention	80–89% retention	< 80% retention
Optional MRI target	≥ 20% of participants have successful MRIs in each group	10–19% of participants have successful MRIs in each group	< 10% of participants have successful MRIs in each group

##### Safety and tolerability

Safety will be assessed by the occurrence of side effects as reported on the systems and NIBS tolerability questionnaires, in addition to the instances and severity of AEs. A correlational analysis will be conducted between the occurrence of side effects and feasibility measures to assess the association between these factors.

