Participants in the active tDCS group will receive a total of 20 min of stimulation per session, at a maximum of 2 mA intensity. For the sham tDCS control group, the same device, montage, and protocol will be used, but the device will be programmed for the sham condition. This condition delivers 30 s of stimulation (max. 1.0 mA) at the start and end of the session to mimic the sensation of the active condition. This is the proven gold standard for participant blinding and sham-control [41–43]. The first treatment session will ramp up to 1.0 mA for all participants. Participants in the sham tDCS group who tolerate 1.0 mA will remain at 1.0 mA in each treatment session. Participants who do not tolerate 1.0 mA will have the current adjusted to 0.75 mA and 1.0 mA will be attempted again at the next session. For the active tDCS group, if 1.0 mA in the first treatment session is tolerated, the second treatment session will begin at 1.5 mA. If 1.0 mA is not tolerated, the session will start at 1.0 mA. If 1.5 mA is tolerated throughout the second treatment session, the third treatment session will begin at 2.0 mA. If 1.0 mA is tolerated throughout the second treatment session, the third treatment session will begin at 1.5 mA. For the remainder of sessions, the intensity tolerated in the final 10 min of one treatment session will serve as the starting point in the next treatment session. If a participant is not tolerating a certain intensity at any point during treatment, it will be reduced by 0.25–0.5 mA, and their symptoms will be re-evaluated at the reduced intensity and adjusted accordingly.

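### Side effects are analysed by occurrence alone although symptoms are rated 1–5, so grade is lost below AE level and in the correlation with feasibility

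*Protocol article*

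**What the plan says.** Under Primary outcome measures, the protocol article names tolerability, with feasibility and acceptability, as a primary objective.

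Data collection is described in two places. Under Safety and tolerability (outcome measures), at each session "a full body 16-item systems questionnaire and the NIBS tolerability questionnaire will be completed by the participant and parent". Under Stopping guidelines, study personnel follow symptoms after stimulation by "having them rate any symptoms on a scale of 1–5". The only use stated for that rating is a stopping trigger: "If any symptoms last longer than 15 min graded at 4 or greater, even upon discontinuing tDCS, stopping protocols will be initiated".

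The analysis is in Data analysis, Safety and tolerability. It says "Safety will be assessed by the occurrence of side effects as reported on the systems and NIBS tolerability questionnaires", and continues "in addition to the instances and severity of AEs". The next sentence is "A correlational analysis will be conducted between the occurrence of side effects and feasibility measures". AEs are graded separately: "All AEs will be evaluated by the study physician for seriousness, severity, expectedness, and relatedness to the intervention".

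The article does not say whether occurrence means ever/never, a number of sessions or a number of items. It gives no expected side-effect rate.

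**The concern.** The analysis section distinguishes two kinds of event in one sentence. AEs are counted and graded; side effects are only counted. Yet the protocol's own stopping trigger treats grade and duration as what separates a tolerable symptom from one that is not. In the planned correlation, a grade 1 symptom and a grade 4 symptom count the same.

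That correlation is the one stated analysis of whether side effects threaten a full trial. If severe symptoms drive missed sessions and mild ones do not, an ungraded measure dilutes the association. A null result could then be read as showing that side effects do not affect adherence or retention. Both are progression criteria in Table 1, which has no tolerability criterion of its own.

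**Working it through.** The plan gives no figure to reproduce here, so the check has three parts.

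**1. What is collected and what is analysed**

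| Information | Collected | Named in the analysis |
|---|---|---|
| Side effect present | Each session, two questionnaires | Yes, as occurrence |
| Symptom grade 1–5 | After tDCS (Stopping guidelines) | No |
| AE severity | Physician rating | Yes |

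The gap is therefore the symptom grade for side effects not recorded as AEs, and for every side effect in the correlation.

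**2. Is occurrence near a ceiling?**

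Inputs: 15 sessions (tDCS intervention) and n = 46 (Sample size). The per-session rate p is an assumption.

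For ever/never with independent sessions, P(ever) = 1 − (1 − p)^15, and the expected number of unaffected children is 46(1 − p)^15:

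| p | P(ever) | Unaffected of 46 |
|---|---|---|
| 0.02 | 0.26 | 34.0 |
| 0.05 | 0.54 | 21.3 |
| 0.10 | 0.79 | 9.5 |
| 0.20 | 0.96 | 1.6 |
| 0.30 | 0.995 | 0.2 |

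Symptoms cluster within children. With a beta-binomial of mean p and within-child correlation ρ, set a = p(1/ρ − 1) and b = (1 − p)(1/ρ − 1). Then P(ever) = 1 − B(a, b + 15)/B(a, b). At ρ = 0.3 this gives 0.41, 0.66, 0.81 and 0.95 for p = 0.10, 0.20, 0.30 and 0.50.

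A count of affected sessions has no such ceiling. At p = 0.30 its mean is 15 × 0.30 = 4.5. Its SD is √(15 × 0.30 × 0.70) = 1.8 with independent sessions, and √(3.15 × (1 + 14 × 0.3)) = 4.0 at ρ = 0.3.

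**3. How much does grade add?**

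Monte Carlo runs used 46 children and 15 sessions, with half the variance of a latent severity lying between children. Symptom-free sessions were coded 1 and symptoms took the higher grades. The chance of missing a session was expit(−3.2 + b(grade − 2)), with slope b = 0.5 or 0.8. At b = 0.5 the chance rises from expit(−3.7) = 0.024 with no symptom to expit(−1.7) = 0.154 at grade 5. At b = 0.8 it rises from expit(−4.0) = 0.018 to expit(−0.8) = 0.310.

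The table gives power at two-sided 0.05 for a Spearman association with sessions completed, over the two slopes:

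| Sessions with any symptom | Share of sessions affected | Mean grade |
|---|---|---|
| 10% | 13–24% | 11–21% |
| 20% | 22–49% | 20–47% |
| 30% | 29–62% | 27–60% |
| 70% | 40–84% | 45–90% |
| 85% | 28–67% | 40–85% |

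The rows at 10–30% assume that 40%, 15% and 5% of symptomatic sessions reach grades 3, 4 and 5 or above. At 50% the mean grade gains about 2 points.

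Ever/never did far worse. In runs with a different grade split it had 10–20% power at a 20% symptom rate (68% of children ever affected) and 6–14% at 30% (81% ever affected). At 70% it had under 1% (99% ever affected). Across rates of 10–85% it did not exceed about 20%.

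Over the grade splits tried, mean grade beat the share by about 3–18 points at symptom rates of 70–85%. At 30% or below it gave no dependable gain and lost up to 5 points.

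**The case against.** The strongest reply is that severity is not ignored. The sentence on occurrence also covers severity of AEs, and the physician rates every AE. A severe symptom recorded as an AE is therefore distinguished in the safety assessment. That is correct, and it limits the point to side effects below AE level and to the correlation.

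Second, how occurrence is aggregated is ordinary detail for an analysis plan that is not shown. This also has force: the open unit alone would not be a finding. But the article does name its analysis variable, and in the same sentence reserves severity for AEs. Following that text discards the grade.

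Third, the simulation makes missed sessions depend on grade, which favours a graded measure. It also ignores the reduction in current after poor tolerance (tDCS intervention), which would alter later grades. Both points stand, so the power figures illustrate and do not predict.

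Fourth, the correlation is exploratory, and no Table 1 criterion, sample size or significance level rests on it. That lowers the weight of the point but does not remove it.

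Three stronger readings are tempting and unsupported:

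- **Almost every child will have an occurrence.** The sham delivers current "at the start and end of the session to mimic the sensation of the active condition", so a reader might infer this. The article gives no rate and does not say how often that sensation would be reported as a side effect.
- **Occurrence cannot separate active from sham.** The simulation has no treatment arm, so this was not tested.
- **Grade should replace occurrence.** The low-rate results above argue against it.

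**Conclusion.** The point holds in a limited form. For a primary objective, the stated side-effect analysis leaves out a grade that the protocol has children rate, and the correlation treats all grades alike.

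The larger loss comes from an ever/never reading, which the text leaves open; most of it is recovered by a per-session share. What grade adds beyond the share depends on symptom frequency, which is unknown. An ever/never ceiling of 95% or more needs a per-session rate of nearly 0.20 with independent sessions, or about 0.50 with within-child correlation 0.3.

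The conclusion about what is discarded rests on the text alone. The sizes rest on assumed symptom rates, grade distributions and slopes, and on coding symptom-free sessions below every symptom, because the article does not define grade 1. They concern sessions completed; retention was not modelled. This is a modest, inexpensive improvement to the analysis and does not invalidate the design.

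**What to change.** In Data analysis, Safety and tolerability:

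1. Define occurrence per child as the share of attended sessions with any side effect. A raw count would rise with attendance itself and so distort the correlation with sessions completed.
2. Beside it, add two graded summaries per child. One is the mean over attended sessions of the worst symptom grade, with symptom-free sessions coded below the lowest symptom grade. The other is the share of attended sessions with any symptom at grade 4 or above, the grade already used in the protocol's stopping trigger.
3. Report the occurrence and graded measures by arm with 95% CI.
4. Give the Spearman correlation of each with sessions completed, and their association with retention, labelled exploratory. At the planned 10% loss only about 46 × 0.10 = 4.6 children would be lost, so the retention result will be imprecise.
5. State what grade 1 means, and confirm that the rating is stored as study data, since it is described only under Stopping guidelines.

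The cost is analysis wording and one or two more derived variables, provided the ratings are recorded. The graded measure may add nothing if symptoms turn out to be infrequent, which is why occurrence stays alongside it.

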##### Device usability and protocol acceptability

Device usability is described by three measures: effectiveness, efficiency, and satisfaction. Effectiveness is determined by the degree of task completion and the total number of errors per task, which will be identified in the training video recordings. Task completion will be coded as follows: (1) completed independently by the user, (2) completed with minor help from the trainer, (3) failed to complete even with help from the trainer. Errors are coded when the user makes mistakes that prevent the continuation of the task without help from the trainer. Efficiency is measured by calculating the average time taken for each task across participants. A table of the tasks and criteria for completion is shown in Table 2. The post-treatment usability survey will assess participants’ satisfaction with the use of the device. The survey includes three sections: “device”, “headband”, and “virtual delivery.” Answers to positive statements are scored positively, and answers to negative statements are scored reversely. The highest possible raw score for each section is 55, 15, and 25, respectively. The raw scores will be converted to a standardized total for each section. A score of 80 or higher will be considered “excellent” as per standard SUS scoring. Users will be given the opportunity to include comments and feedback on each section.

**Table 2 Tab2:** Task analysis and completion criteria for tDCS device use

Task	Task completion criteria
**Place batteries into device**	Correct orientation of batteries
**Put sponges on headband**	Correct orientation of sponges
	Securely attached to headband
**Plug headband into device**	Correct color wire into the correct color port (red-red, black-black)
**Turn on device**	Pressed correct button
**Initiate “stimulation” setting**	Pressed correct button
**Place headband on participant**	Correct orientation of headband
	Remove hair underneath sponges
	Contact quality: Good

The pre-treatment usability survey provides information on the general technological knowledge and ability of the person administering the tDCS. This score will be correlated with the score on the post-treatment survey to provide insight into how varying levels of technological knowledge may impact the usability experience of the tDCS device.

#### Secondary measures analysis

A modified intent-to-treat analysis will be used for secondary data. Analyses of secondary measures will only include participants who have provided data at baseline and at least one follow-up timepoint.

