#### Eligibility

Self-regulation impairment will be defined by a score of four or greater on items 4 (disruptive behavior) or 5 (restricted and repetitive behavior) on the Clinical Global Impressions Severity (CGI-S) administered by a physician during screening [27]. As this is a feasibility study, there will be no intelligence quotient (IQ) cut-off for participation. It is critical that novel treatments for response inhibition and self-regulation be studied in the broader autism community, as children with lower IQs more frequently exhibit social impairments and self-regulation challenges [28, 29], and are not typically candidates for behavioral treatments that require high learning demands and cognitive effort. Children with safety contraindications for tDCS (e.g., seizure disorder), magnetic resonance imaging (MRI) (e.g., metal in situ), or co-morbid neurological disorders (e.g., epilepsy, stroke, brain tumor) will be excluded. Children must not have had any changes to their medications for at least 6 weeks prior to the baseline assessment (T0) and no planned medication changes during the study. Children with prior tDCS experience will be excluded to ensure blinding.

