##### Clinical and cognitive

For clinical assessments and the Go/No Go task, between-group differences over time will be examined using a linear mixed-effects model approach. Follow-up scores for each outcome will be included as dependent variables, and baseline and treatment allocation values will be included as fixed-effect predictors. Time points will be included as a fixed factor. To account for the correlation between repeated measurements from the same participant, a random intercept will be included at the participant level.

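### Requiring a baseline value leaves a child with Go/No Go follow-up scores but no T0 score out of that analysis; a missing-baseline indicator would keep the child at almost no cost

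*Protocol article*

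**What the plan says.** Under Secondary measures analysis the Protocol article states "A modified intent-to-treat analysis will be used for secondary data" and defines the set: "Analyses of secondary measures will only include participants who have provided data at baseline and at least one follow-up timepoint". It does not say whether baseline data means any baseline data or a baseline value on the outcome being analysed.

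Under Clinical and cognitive, which covers the clinical scales and the Go/No Go task, the model is described as follows: "Follow-up scores for each outcome will be included as dependent variables, and baseline and treatment allocation values will be included as fixed-effect predictors". Baseline is thus a covariate, not a response, and nothing is said about a child whose baseline value is absent.

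Three other places bear on how likely that is:

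- **Eligibility:** "As this is a feasibility study, there will be no intelligence quotient (IQ) cut-off for participation", with the reason that "It is critical that novel treatments for response inhibition and self-regulation be studied in the broader autism community".
- **Cognitive:** "This specific Go/No Go task was chosen due to its simplicity and ability to be understood by individuals with a wide range of IQs and" (the sentence goes on to name the severity of autism as well).
- **Data analysis, Feasibility:** the article plans to relate participant characteristics, IQ among them, to whether a child manages every task in the trial.

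**The concern.** In a randomised comparison the baseline score improves precision, but a child's follow-up outcome is informative about treatment without it. Deleting an observed follow-up score because a covariate is missing throws away randomised information, and a simple, accepted method avoids this.

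The Go/No Go is the outcome where it could matter, because it needs performance from the child, whereas the CGI is a physician interview and the ABC, EDI, AIM and ERC are parent reports. Children who give no valid T0 score may tend to be those of lower ability, the group that the open IQ criterion was meant to let in. At stake are some precision in a small trial and how far the Go/No Go estimate speaks for that group.

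**Working it through.** **Does the exclusion follow from the text?** There are two readings of the analysis-set rule.

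1. Baseline data means a value on the same outcome. A child without a T0 Go/No Go score then fails the rule for that outcome.
2. Baseline data means any data. The child then passes the rule, but the model needs a T0 Go/No Go value as a fixed-effect predictor, so as written the child still cannot enter.

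The child is left out of the Go/No Go analysis either way.

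**Inputs for the size**

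- Randomised: 46, with 10% expected loss to follow-up (Sample size). 46 × 0.9 = 41.4, so about 41 retained.
- Share with no T0 score but usable follow-up: not given. Assumed 5%, 10% and 15% of 41, that is k = 2, 4 and 6.
- Correlation ρ between baseline and follow-up: not given. Assumed 0.6, with 0.4 and 0.8 as a range.

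The article states no figure on this point, so there is none to reproduce.

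**Formulas** (one follow-up value per child, relative to all 41 having a baseline)

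- Dropped: SE ratio = √(41 / (41 − k)).
- Kept without baseline: such a child has residual variance σ² instead of σ²(1 − ρ²), and so counts as 1 − ρ² of a full child. SE ratio = √(41 / (41 − k + k(1 − ρ²))).

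| k | Dropped | Kept, ρ = 0.4 | Kept, ρ = 0.6 | Kept, ρ = 0.8 |
|---|---|---|---|---|
| 2 | √(41/39) = 1.025 | √(41/40.68) = 1.004 | √(41/40.28) = 1.009 | √(41/39.72) = 1.016 |
| 4 | √(41/37) = 1.053 | √(41/40.36) = 1.008 | √(41/39.56) = 1.018 | √(41/38.44) = 1.033 |
| 6 | √(41/35) = 1.082 | √(41/40.04) = 1.012 | √(41/38.84) = 1.027 | √(41/37.16) = 1.050 |

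At ρ = 0.6 the avoidable inflation is 2.53 − 0.89 = 1.6 percentage points for k = 2 and 8.23 − 2.74 = 5.5 for k = 6. At ρ = 0.8 it is about 0.9 and 3.2. The kept columns are slightly optimistic for very small k: if both of two such children fall in the same arm, the indicator absorbs them and they add nothing.

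**Bias check by simulation** (4,000 replicates, 42 children, 1:1, assumed effect 0.5, ρ about 0.6, baseline missing in the lowest-ability children)

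| Share missing | Dropped: mean (SD) | Kept with indicator: mean (SD) | SD ratio |
|---|---|---|---|
| 10% | 0.500 (0.272) | 0.502 (0.260) | 1.046 |
| 20% | 0.501 (0.279) | 0.502 (0.257) | 1.086 |
| 30% | 0.506 (0.306) | 0.505 (0.273) | 1.121 |

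With a common effect neither approach is biased, and dropping is less precise. If the effect in the children without baseline is instead assumed to be 1.0, dropping them still returns about 0.50, the effect in those retained. The effect over all randomised children is then 0.56, 0.61 and 0.66, and keeping them gives 0.55, 0.60 and 0.65. The doubled effect is an illustration only; nothing in the article supports it.

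**The case against.** The strongest reply is that the premise is conjecture. The article nowhere expects a child to fail the task at T0 and manage it later, and it says the task was chosen for simplicity across IQ levels. A child unable to do it at T0 will often be unable at T1 and T2 too, and then no analysis recovers anything. This stands, and it makes 2 to 6 children an upper scenario under that mechanism. It does not make the case impossible: the planned analysis relating IQ to task completion treats non-completion as an open question.

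Three stronger readings are tempting, and the documents do not support them.

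- **That such children are discarded from the trial.** The rule covers secondary measures only. Recruitment, retention, adherence, tolerability and usability are unaffected, and if the rule works outcome by outcome the child stays in the CGI and parent-reported analyses.
- **That the treatment comparison is biased.** T0 precedes stimulation and assessors are blinded, so a missing T0 score should not depend on arm.
- **That most of the lost information is always recoverable.** The recovered share is simply 1 − ρ²: 0.64 at an assumed 0.6, but only 0.36 at 0.8.

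The stakes are also low. The article says that pilots do not test efficacy, calls the secondary analyses exploratory, and bases no progression criterion in Table 1 on the Go/No Go.

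**Conclusion.** The point holds as a minor one. The stated rule and the baseline-covariate model together leave out of the Go/No Go analysis a child whose randomised follow-up scores are known. Under the assumed 5–15% of about 41 children and ρ = 0.6, the avoidable cost is about 1.6 to 5.5 percentage points of standard error, and less if ρ is higher. The estimate stays valid for the children retained; what suffers is modest precision and how well the result represents lower-ability children.

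A reader might infer that the rule defeats the purpose of the open IQ criterion. That goes too far: the criterion is justified by the feasibility aim, which the primary outcomes serve whether or not a child has a T0 task score. Both the rate of missing T0 scores and their concentration in lower-ability children are assumptions.

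**What to change.** For the outcomes analysed with the mixed model, state that the rule applies outcome by outcome. Wording along these lines would do: *each outcome is analysed in all randomised participants with at least one follow-up value on it; a missing baseline is set to the mean over both arms combined, and an indicator for missing baseline is added as a fixed effect.* The rest of the model stays as it is.

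A constrained longitudinal model, with T0, T1 and T2 as responses and a common T0 mean in both arms, may serve as a sensitivity analysis. It treats the absent T0 score as missing at random, which is strained if the reason is inability to do the task, so that assumption should be noted.

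Report by arm and visit how many children could not perform the Go/No Go. This also feeds the planned analysis of IQ and task completion.

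The cost is a sentence or two of wording and a few lines of code, with no new data.
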